### Design

AZTEC is a double-blind, randomised, placebo-controlled trial using azithromycin or placebo as previously described [27]. The AZTEC-FU study will continue to follow-up the infants recruited to AZTEC up to 2 years of corrected age. The participants and researchers will continue to remain blinded for the AZTEC-FU study.

Data between 36 weeks’ PMA and discharge from the neonatal unit are collected from a dedicated discharge clinical record form (CRF), neonatal discharge summaries and clinic letters, data held in the National Neonatal Research Database (NNRD) and from the parents. When the infants enrolled in the AZTEC trial reach 1-year and 2-years of corrected age, we are contacting the parents/guardians by mailing them validated (a) respiratory and (b) neurodevelopmental questionnaires. In addition, we are asking the parents/guardians for (c) information on any hospital admissions and (d) growth data of their babies from the Red Book system in the UK, which records growth data by Health Visitors, and at local hospital follow-up clinics. An option is available to complete the questionnaire on a secure online site. In parallel, we are contacting local hospitals for clinic letters from which relevant data are extracted: including (a) respiratory symptoms, (b) developmental progress, (c) growth, (d) hospital admissions, and (e) any medication especially respiratory and antibiotic usage. In addition, we are also contacting the General Practitioners for clinic letters, discharge summaries and a copy of the GP record for the children to provide an additional route to collect the above information. Data will also be obtained from NHS Digital for information on hospital admissions and outpatients’ attendances and from the data held in the National Neonatal Research Database (NNRD) at Imperial College, a central repository where most of the UK neonatal units send their clinical data [30] (Fig. 2).

**Fig. 2 Fig2:**
[figure not shown]
Flow Chart of Process

### Patient and public involvement

Input from parents of preterm-born children was given during the grant application on the design and conduct of the study and parents were part of the Trials Management Group and Trials Steering Committee. Parents with previous preterm-born children as well as senior neonatal nurses and doctors also reviewed the information sheets and questionnaires. Amendments were made after their input.

### Setting

Infants have been enrolled on the AZTEC trial from 28 tertiary neonatal units and approximately 77 step-down units in the UK. Where parental consent permits, they are being followed up at 1 and 2 years of corrected age.

### Inclusion criteria

Participation in the AZTEC trialSurvival at 36 weeks’ PMAConsent provided by the parents/guardians to be contacted for follow-up at 1 and 2 years of corrected age

### Exclusion criteria

Withdrawal from AZTECParents/guardians did not provide consent to follow-up at 1 and 2 years corrected ageDeath prior to 36 weeks’ PMAPost-discharge survival not confirmed

### Trial intervention

As previously described [27], infants born at < 30 weeks’ gestation, within 72 h of birth, were treated intravenously for ten days with 20 mg/kg azithromycin for 3 days, followed by a further 7 days of 10 mg/kg or with similarly constituted and administered placebo.

### Trial procedures

#### Site selection and training

Tertiary and step-down units who were involved in AZTEC have been invited to participate. Sites only need to provide copies of clinic letters and discharge summaries; thus, no formal training is required.

#### Participant recruitment

During the AZTEC trial, the AZTEC-FU study is also discussed, and written informed consent is obtained from the parents/guardians for follow-up to 2 years of corrected age.

#### Screening and consent

Eligible infants were screened postnatally against the inclusion and exclusion criteria as previously described [27]. At the initial consent procedure for inclusion in the AZTEC study, the parents/guardians optionally consented to follow-up at 1 and 2 years of corrected age with an additional option to contact the infant’s general practitioner (GP). In addition, the parents/guardians optionally consented for their babies’ data to be reviewed on relevant databases such as NHS Digital and data held in the NNRD. Any participant withdrawals or deaths during the initial neonatal unit stay are communicated by the AZTEC team to the AZTEC-FU study team. Continued consent is also presumed if the parents/guardians complete and return the completed questionnaire at 1 and 2 years of corrected age. The parents/guardians have the right to withdraw from the study at any time without affecting their infant’s clinical care is clearly communicated.

#### Randomisation

The recruited infants were randomised to either active treatment or placebo as previously described [27]. Double blinding is being maintained for the AZTEC-FU study.

#### Data collection

All collected data are securely and confidentially stored with restricted access on Cardiff University servers according to the university’s security policy.

#### Questionnaires at 1- and 2-year’s corrected age

For those who consented to follow-up, a questionnaire including a covering letter explaining the study, an information sheet explaining the questionnaire, a stamped questionnaire return envelope and a voucher to thank the parents for their baby’s participation in the study are mailed. The letter also contains a personalised quick response (QR) code and website URL link which they can use if they wish to complete the questionnaire via a secure online website (Online Surveys, Jisc, Bristol, UK).

The questionnaire at 1-year corrected age captures respiratory symptoms, the infant’s and family history of atopy, number of course of antibiotics, number of hospital admissions, maternal smoking during pregnancy and current smoking in the family who share the house with the infant, information on siblings, as well as general developmental questions and entries for the infant’s weight, length/height and head circumference. The questionnaire also specifically asks if the infant has had pyloric stenosis [21].

At 2 years of corrected age, the questionnaire captures the same information as year one, but with greater detailed neurodevelopment data captured via using the PARCA-R questionnaire which has been validated against Bayley’s Scales of Infant Development Version III assessments [31].

#### Data from general practitioners

At 1 and 2 years of corrected age for the infants whose parents/guardians have consented to the AZTEC-FU study, the GPs are contacted for copies of the infant’s notes including medical or surgical consultations, hospital discharge summaries and outpatient clinic or in-patient letters. Data is being extracted from these records by the AZTEC-FU study team including information on number of hospital admissions, diagnoses, duration of home oxygen therapy (if applicable) and drug history.

Data held in the NNRD which collates neonatal data provided for each neonatal admission by almost all neonatal units in the UK. Data collected includes information on initial neonatal admission as well as neurodevelopmental data at 2 years of corrected age, most commonly assessed by using Bayley’s Scales of Infant Development Version III, but during and after the COVID-19 pandemic many units are increasingly using PARCA-R as a screening tool. Data held in the NNRD is being provided annually for each infant recruited to the AZTEC trial for infant’s whose parents/guardians have provided appropriate consent.

#### NHS digital

It is anticipated that data for infants recruited to the AZTEC trial can be obtained from NHS Digital, once the relevant permissions have been obtained for infants whose parents/guardians have provided appropriate consent for access to the infant’s data from relevant databases. NHS Digital data should provide additional and confirmatory data obtained from the various sources outlined above including hospital and general practitioner records.

#### Hospital data

At 1 and 2 years corrected age, the infant’s local hospital is being contacted if we have the relevant consent from the parents/guardians to supply the infant’s hospital discharge summaries and clinic letters.

The local hospital is being identified from the infant’s address and from information from the recruiting hospital and the step-down hospitals. This information is requested from each local principle investigator when the infants reach 1 and 2 years of corrected age.

### Data analysis

#### Sample size

The initial sample size was calculated for the main AZTEC trial: for 12% improvement of survival without CLD, with an alpha of 0.05 and power of 0.90, would require 796 including 10% drop out. The study recruitment completed in March 2022 recruiting 799 infants. For the current study, the power available will depend on returns of questionnaires and collection of data from a wide variety of sources. Mortality between 36^+1^ weeks and 1 year of corrected age is estimated to be < 5% (with negligible occurring in the second year) and the baseline wheezing rate at 1 year of corrected age for children born ≤ 30 weeks’ gestation is estimated at 60–65% [6] and 50–55% for moderate/severe neurodevelopmental disability at 2 years of corrected age [28, 29]. The tables show the effect size for the parent-reported wheezing at any time during first year of life (Table 1) and for survival without developing moderate/severe neurodevelopmental at 2 years corrected age (Table 2) at an alpha of 0.05 and power of 0.80 and 0.90. It is reasonable to expect approximately 70–75% outcome data from the anticipated 700–725 survivors at 36 weeks’ PMA for the follow-up studies, i.e. approximately 500. These should be able to detect differences of 12.7% at power of 0.80 and alpha of 0.05 for parent reported wheezing at 1-year corrected age between the azithromycin and placebo groups. A similar 12.7% difference should be detectable for in survival without developing moderate/severe neurodisability at 2 years of corrected age between the two treatment arms.

**Table 1 Tab1:** Estimated effect size for respiratory outcome (wheeze at any time during first year of life) for anticipated questionnaire returns

Size per group	Prevalence of wheezing after treatment	Detectable effect size
**Power 0.8, alpha 0.05, initial incidence of wheeze 65%**		
350	54.3%	10.7%
300	53.5%	11.5%
250	52.3%	12.7%
200	50.7%	14.3%
**Power 0.9, alpha 0.05, initial incidence of wheeze 65%**		
350	52.7%	12.3%
300	51.7%	13.3%
250	50.4%	14.6%
200	48.5%	16.5%

**Table 2 Tab2:** Estimated effect size for neurodevelopmental outcome (survival at 2 years without moderate/severe neurodevelopmental impairment) for anticipated questionnaire returns

Size per group	Survival without moderate/severe neurodevelopmental impairment	Detectable effect size
**Power 0.8, alpha 0.05, initial incidence of survival without moderate/severe neurodevelopmental impairment of 50%**		
350	60.7%	10.7%
300	61.6%	11.6%
250	62.7%	12.7%
200	64.4%	14.6%
**Power 0.9, alpha 0.05, initial incidence of survival without moderate/severe neurodevelopmental impairment of 50%**		
350	62.3%	12.3%
300	63.3%	12.3%
250	64.6%	14.6%
200	66.4%	16.4%

#### Statistical analysis

A statistical analysis plan will be developed prior to the end of the study. Baseline descriptors will be given. Data analyses will be conducted to identify any differences in the respiratory, neurodevelopmental, and growth outcomes, as well as hospital admissions between the placebo and the treatment group using two-by-two tables and chi-square testing. We shall consider *p* < 0.05 as statistically significant and report 95% confidence intervals. We shall also model the data, as in our previous publications [6], to identify early life factors that may result in long-term respiratory/neurodevelopmental abnormalities including presence/absence of *Ureaplasma* spp. at baseline before intervention commenced in the neonatal period; and if the treatment effect is influenced by early life factors, e.g. gestation, sex, and use of mechanical ventilation. Initially, we shall report the univariable data with a view to including any relevant factors into a model (using linear or logistic regression as appropriate). Missing data will be included in the analysis as missing data.

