
Neurodevelopmental outcome following preterm birth is a key metric for parents and the neonatal community [39]. Preterm birth is inherently associated with increased risk of poorer neurodevelopment [11, 12], with a strong association, and shared risk factors, between CLD and functional and cognitive outcomes [15]. Human studies have shown that azithromycin is widely distributed in the brain tissue [40], with animal models suggesting that azithromycin may also confer neuroprotective benefits. However, human data for the neuroprotective efficacy of azithromycin is currently lacking. Whilst we postulate improved neurodevelopmental outcomes at 2-year corrected age for those infants treated with azithromycin, we shall also investigate if there are detrimental neurodevelopmental effects from the early use of early azithromycin by using two-tailed comparisons. With our anticipated 500 responses, we have estimated that we should be able to detect 12.7% differences for the main respiratory and neurodevelopmental outcomes at 1 and 2 years of corrected age respectively.

The AZTEC-FU studies are also monitoring survival up to 2 years of age, separately reporting deaths at important timepoints up to 2 years of corrected age. Growth is another important postnatal factor, with preterm infants having poorer inpatient growth velocities [41], and those with CLD were noted to have poorer growth once discharged home [16]. We are collecting anthropometric measurements, including weight, length and head circumference at discharge, and over the first 2 years of life from routine clinic appointments and health visitor assessments. If azithromycin proves effective at reducing rates of CLD, it will be important to assess whether that confers growth benefits following discharge home.

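### The named analyses treat infants as independent although siblings from one pregnancy are not excluded; depending on how siblings were allocated, the main tests can be miscalibrated

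*Protocol article*

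**What the plan says.** Under Statistical analysis, the article compares respiratory, neurodevelopmental and growth outcomes and hospital admissions between the arms "using two-by-two tables and chi-square testing". It takes p < 0.05 "as statistically significant and report 95% confidence intervals", and the Discussion says that the neurodevelopmental question will be examined "by using two-tailed comparisons". The same section plans linear or logistic regression to identify early-life factors and to see whether gestation, sex or mechanical ventilation modify the treatment effect. Secondary analysis adds baseline Ureaplasma as an interaction term for both main outcomes.

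The unit counted throughout is the infant: "The study recruitment completed in March 2022 recruiting 799 infants". About 500 are expected to provide outcome data, of whom the Sample size section says: "These should be able to detect differences of 12.7% at power of 0.80 and alpha of 0.05".

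The inclusion and exclusion criteria say nothing about multiple births, and the Randomisation section refers to the parent trial's protocol for the method. The article mentions neither clustering nor robust or mixed-model variance. Its only reference to siblings is a questionnaire item, "information on siblings".

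**The concern.** A chi-square test and an ordinary regression take each infant's outcome as independent of every other's. Siblings from one pregnancy share a mother, a household and gestational age, and the same parent would usually complete their wheeze and PARCA-R forms. Positive correlation within a pregnancy is therefore plausible for both main outcomes.

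The consequence for the between-arm tests depends on allocation. If siblings share an arm, the usual standard error is too small and the test rejects too often. If they are always in opposite arms, the standard error is too large and the test is conservative. If each infant is randomised separately, same-arm and split pairs balance on average. For a covariate that siblings share by definition, such as gestation, the allocation rule is irrelevant: the ordinary standard error is too small whenever the correlation is positive.

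At stake are the stated 5% level and 95% intervals for the two main outcomes, the Ureaplasma subgroup estimates, and the claims about which early-life factors matter.

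**Working it through.** **Inputs from the article.** Two-sided alpha 0.05, power 0.80, 250 per group. Wheeze 65% against 52.3% (Table 1). Survival without moderate/severe impairment 50% against 62.7% (Table 2). Stated difference d = 12.7 points for both.

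**Inputs assumed, not in the article.** Share of infants in sibling pairs s = 0.20-0.30; within-pair correlation rho = 0.2-0.5.

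**Step 1: reproduce the stated figure.** Per-group size for two proportions, with p̄ the mean of p1 and p2:

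n = [1.96·√(2p̄(1−p̄)) + 0.8416·√(p1(1−p1) + p2(1−p2))]² / d²

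- Wheeze: (1.365 + 0.581)² / 0.127² = 235.
- Survival without impairment: (1.375 + 0.585)² / 0.127² = 239.

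With the continuity correction, n' = (n/4)·[1 + √(1 + 4/(n·d))]², these become 251 and 254, against 250 stated. The 12.7 points are therefore an ordinary continuity-corrected calculation for independent infants, with no design effect.

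**Step 2: design effect (DE) for the between-arm comparison.** DE = 1 + c·s·rho, where c = +1 if pairs share an arm, about 0 if each infant is randomised independently, and −1 if pairs are always split. The true size of the nominal 0.05 test is 2·[1 − Φ(1.96/√DE)].

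| Allocation | s, rho | DE | True size |
|---|---|---|---|
| Same arm | 0.20, 0.2 | 1.04 | 0.055 |
| Same arm | 0.30, 0.5 | 1.15 | 0.068 |
| Independent | any | about 1.00 | about 0.050 |
| Split | 0.20, 0.2 | 0.96 | 0.046 |
| Split | 0.30, 0.5 | 0.85 | 0.034 |

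A simulation of 500 infants at a null rate of 65% (20,000 runs per setting) agrees. At s = 0.30 and rho = 0.5, the chi-square rejected in 0.067 of runs with siblings in the same arm, 0.050 with independent allocation and 0.035 with siblings split.

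**Step 3: detectable difference if siblings share an arm.** Detectable difference = 12.7·√DE; effective sample = 500/DE.

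- DE 1.04: 12.7 × 1.020 = 13.0 points; effective sample 481.
- DE 1.15: 12.7 × 1.072 = 13.6 points; effective sample 435.

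**Step 4: power at 250 per group if siblings share an arm.** Let se0 and se1 be the null and alternative standard errors of the difference.

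- Ordinary uncorrected chi-square: power = Φ[(d − 1.96·se0)/(se1·√DE)]. For wheeze, se0 = 0.0440 and se1 = 0.0437, giving 0.824 at DE 1.00, 0.819 at 1.04 and 0.807 at 1.15. For survival without impairment the values are 0.819, 0.814 and 0.802.
- A test whose standard error is inflated to hold the 5% level: 0.809 and 0.769 for wheeze, 0.804 and 0.763 for survival without impairment, at DE 1.04 and 1.15.

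**Step 5: regression on a pregnancy-level factor.** Siblings share gestation exactly, so the variance inflation for its coefficient is 1 + s·rho whatever the allocation rule. At s = 0.30 and rho = 0.5 this is 1.15, and the nominal 0.05 test has size 0.068. A simulation with a covariate shared within pairs (500 infants, 20,000 runs) also gave 0.068.

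**The case against.** Four objections deserve an answer.

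**The article does not show that the p-values are wrong.** A reader might infer that the chi-square test is invalid for any non-zero share of multiples, or that the reported p-values and intervals must be wrong. The article does not support that. It says neither that siblings were co-enrolled nor how they were allocated, and the questionnaire item on siblings is no evidence of either. Its wording that infants were randomised is compatible with independent allocation, under which the test stays near 5%. This objection stands, and it makes the point about the main comparisons conditional.

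**Power need not fall below 0.80.** A reader might also infer that same-arm siblings take the planned test below its stated power. Step 4 shows otherwise: the ordinary chi-square keeps about 0.80-0.82, because the published figure already carries a continuity correction. It does so while exceeding its 5% level; a test that holds that level has about 0.76-0.81. If the analysis also used a continuity correction, part of the excess in size would disappear.

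**Variance estimation for multiples is usually SAP material.** The article says that a SAP will follow, and that SAP may already cluster. Silence alone would be no finding. But the article does not leave the test open: it names one that assumes independence. A SAP that clusters would depart from this text, and a SAP that follows it would inherit the problem.

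**Regression is planned as well.** An interaction term needs a model, so the chi-square is not the only analysis. That is true, but the models are described as ordinary linear or logistic regression, which makes the same independence assumption.

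**Conclusion.** The concern holds in conditional form and is moderate in size. The article commits the between-arm comparisons and the early-life-factor models to methods that assume independent infants, in a population where siblings from one pregnancy are to be expected and are not excluded. The planning figure makes the same assumption.

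For the main comparisons, the direction and size of any error depend on an allocation rule that the article does not give. Under the assumed ranges, size runs from about 0.034 (split, upper end) through 0.05 (independent) to about 0.068 (same arm, upper end). For regressions on pregnancy-level factors, the understatement of standard errors does not depend on that rule, only on there being co-enrolled siblings with positively correlated outcomes. The share of pairs and the correlation are assumptions throughout and should be replaced by the trial's own figures.

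**What to change.** - State how many enrolled infants have an enrolled sibling from the same pregnancy, and how such siblings were allocated.
- Analyse both main outcomes, the Ureaplasma interaction models and the early-life-factor models by regression that clusters on pregnancy: GEE with robust variance, or regression with cluster-robust standard errors.
- Report the risk difference and its 95% confidence interval from that model, and keep the two-by-two tables as description.
- If siblings were allocated to the same arm, restate the 12.7-point detectable difference with the design effect from the actual share of multiples.

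The cost is minor: a pregnancy identifier, which the trial should already hold, a little more analysis work, and possibly a slightly less favourable stated figure. No new outcome data are needed. If each infant was randomised independently, clustering costs almost nothing in the main comparisons and still corrects the models of pregnancy-level factors.

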### Secondary analysis

Presence of *Ureaplasma* spp. at baseline (i.e., before randomisation) will be added as an interaction term for the main analyses of parent reported wheezing at 1-year corrected age and for survival without development of moderate/severe neurodevelopmental disability at 2-year corrected age. Main effects and interactions will be reported, as well as the *p*-value for the interaction term. Subgroup-specific estimates (with accompanying 95% confidence intervals) for each outcome will also be derived from model estimates.

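### One univariable-first step serves both the search for prognostic factors and the search for effect modifiers; it suits the second badly and encourages selective reporting in the first (minor, secondary analyses only)

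*Protocol article*

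**What the plan says.** All of this stands in the protocol article under Data analysis.

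- **Main treatment comparison** (Statistical analysis): made "using two-by-two tables and chi-square testing". No covariates enter it.
- **Significance rule** (Statistical analysis): "We shall consider *p* < 0.05 as statistically significant". The Discussion adds that comparisons are two-tailed.
- **First aim of the models** (Statistical analysis): "to identify early life factors that may result in long-term respiratory/neurodevelopmental abnormalities".
- **Second aim** (Statistical analysis): to see "if the treatment effect is influenced by early life factors, e.g. gestation, sex, and use of mechanical ventilation". The factors are examples, not a closed list.
- **Route into the models** (Statistical analysis), given once for both aims: "Initially, we shall report the univariable data with a view to including any relevant factors into a model". Linear or logistic regression then follows, according to the outcome.
- **Secondary analysis**: baseline Ureaplasma "will be added as an interaction term for the main analyses of parent reported wheezing at 1-year corrected age", and likewise for the main neurodevelopmental outcome. Main effects, the interaction p-value and subgroup-specific estimates are promised. No univariable step is attached.

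The same section says that a statistical analysis plan is still to be written.

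**The concern.** A univariable screen asks whether a factor is associated with outcome when treatment arms are pooled. Effect modification is a different question: whether the treatment difference varies across levels of the factor. The two can come apart completely. If a factor raises risk in one arm and lowers it in the other, its pooled association can be nil, and a screen discards it before any interaction is examined.

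For the prognostic aim the issue is reporting. If the same roughly 500 infants choose the factors and then supply their estimates, and only the chosen factors are shown, weak factors appear mainly when chance has enlarged them.

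At stake is how far the secondary models can be trusted on which factors matter and for whom treatment works differently. The main treatment comparison is not at stake.

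**Working it through.** **Inputs from the article.** About 500 infants with outcome data; 250 per group; wheeze 65% without treatment against 52.3% with treatment (Sample size and Table 1); two-sided alpha 0.05.

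**Inputs assumed, because the article gives none.** A screen at p < 0.05; a two-level factor present in half the infants, giving 500/4 = 125 per treatment-by-factor cell; the cell risks below; the number and strength of candidate factors.

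**Step 1: the plan's own figure.** For 65% against 52.3% at power 0.80,

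n = [1.96√(2p̄(1−p̄)) + 0.842√(p₁(1−p₁) + p₂(1−p₂))]² / d², with p̄ = 0.5865 and d = 0.127,

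n = (1.365 + 0.581)² / 0.01613 ≈ 235 per group.

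The continuity correction, (n/4)(1 + √(1 + 4/(nd)))², gives 251. The stated 250 per group for 12.7 points is reproduced.

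**Step 2: effect modifiers.** The interaction on the log-odds scale is i = L(treated, F+) − L(treated, F−) − L(placebo, F+) + L(placebo, F−), where L is the logit of the cell risk. SE² = Σ 1/[125 p(1−p)] over the four cells, and power ≈ Φ(|i|/SE − 1.96).

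| Scenario | Placebo F−, F+ | Treated F−, F+ | Pooled risk F−, F+ | \|i\| / SE | Power by formula | Power, simulated | Passes screen, simulated |
|---|---|---|---|---|---|---|---|
| A. Opposite 15-point effects | 50%, 65% | 65%, 50% | 57.5%, 57.5% | 1.238 / 0.367 | 92% | 93% | 5% |
| B. 25.4-point effect in F+ only, balanced margins | 60%, 72.7% | 60%, 47.3% | 60%, 60% | 1.088 / 0.373 | 83% | 84% | 5% |
| C. 25.4-point effect in F+ only, equal placebo risk | 65%, 65% | 65%, 39.6% | 65%, 52.3% | 1.041 / 0.373 | 80% | 80% | 83% |

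The simulations used 20,000 runs each. A separate simulation put the interaction power for modifiers without a marginal association at 86 to 94%, so 84 to 94% is a fair range.

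In B the average treatment effect is 25.4/2 = 12.7 points, the plan's own detectable difference, and the screen still removes the factor about 95% of the time. In C the factor usually survives, yet passing the screen and then showing a significant interaction happens in 67% of runs, against 80% for the interaction test alone.

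**Step 3: prognostic factors.** With k independent null candidates, the chance that at least one passes at p < 0.05 is 1 − 0.95^k: 23%, 40%, 54% and 64% for k = 5, 10, 15 and 20.

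To see whether this harm belongs to screening, the screen was set against a full model: n = 500, 15 candidates of which 12 are pure null, one true odds ratio of 1.2 per SD, 1,000 runs.

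| | Screen, then model | Full model |
|---|---|---|
| At least one pure-null factor significant in the model | 34% | 46% |
| Mean odds ratio for the 1.2 factor, when kept (screen) or significant (full model) | 1.31 | 1.32 |
| Interval coverage for the 1.2 factor | about 95% | about 95% |

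The 46% is what 1 − 0.95^12 gives. The inflation is as large when significant factors are picked from a full model, so it comes from showing results because they are significant. It also fades with strength: for a two-level factor at n = 500, a true log odds ratio of 0.2 averages 0.46 when kept (2.3 times too large), while 0.6 averages 0.64 (1.07 times).

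**The case against.** The strongest reply is that the article never states a statistical entry rule. Relevance could mean clinical relevance; the p < 0.05 sentence follows the treatment comparisons and is not offered as a threshold for entry. The modelling is said to follow earlier publications that are not available here, and candidate lists and entry criteria are usual content of an analysis plan still to be written. This stands in part. The threshold used above is an assumption, and a reader who infers that the article fixes a p < 0.05 screen goes beyond the text. What the article does state is an order of work, univariable results first and inclusion in light of them, and its ordinary meaning is screening. An analysis plan that followed the sentence faithfully would carry the difficulty forward.

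Second, nothing says that gestation, sex or ventilation must pass a univariable test before their interactions are examined, and the Ureaplasma interaction is expressly free of one. Both are true. The article therefore cannot be said to defeat its second aim; it gives that aim one route that may discard what it looks for, while handling Ureaplasma without it.

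Third, scenarios A and B were built to have no marginal association. That is fair, and it is why C is shown beside them.

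Fourth, a reader might infer from the chance-entry and inflation figures that screening does harm that a full model avoids. The comparison in step 3 does not support that: a full model read only for its significant factors does no better.

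**Conclusion.** The concern holds in a limited form. Using univariable results as the gateway to the models is a poor way to look for effect modification: modifiers with no marginal association would pass about 5% of the time against 84 to 94% for a direct test, while one that also shifts marginal risk would pass about 83% of the time. For prognostic factors the fault is selective reporting of weak effects (1.2 read as about 1.31), and the remedy is to report every pre-listed factor, not merely to drop the screen.

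These sizes rest on an assumed p < 0.05 screen, 125 infants per cell and the effect sizes shown. A reader might infer that the main results are compromised. They are not: the chi-square comparisons use no selected covariates, and the Ureaplasma interaction is pre-specified. Severity is minor and confined to secondary analyses.

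**What to change.** In the analysis plan:

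1. For each main outcome, fit one model with a short list of factors set in advance on clinical grounds, for example treatment, gestation, sex and baseline Ureaplasma. Keep and report all of them whatever their result.
2. Present univariable results as description only, not as the route into the model.
3. Test the modifiers that the article names by pre-listed treatment-by-factor interactions with no univariable screen, as the Secondary analysis section already does for Ureaplasma. These are gestation, sex and, where its status is recorded before randomisation, mechanical ventilation.
4. Label any wider search for factors as exploratory.

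The sample can carry this. At 60 to 65% wheeze, 500 infants include 500 × 0.35 = 175 to 500 × 0.40 = 200 without wheeze, which at ten per parameter (a rule of thumb) supports about 17 to 20 parameters.

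The change is one of wording, with no new data. Its cost is slightly wider intervals from factors that turn out not to contribute.
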